## Abstract

**Background:**

Cluster-C personality disorders (PDs) are highly prevalent in clinical practice and are associated with unfavourable outcome and chronicity of all common mental health disorders (e.g. depression and anxiety disorders). Although several forms of individual psychotherapy are commonly offered in clinical practice for this population, evidence for differential effectiveness of different forms of psychotherapy is lacking. Also, very little is known about the underlying working mechanisms of these psychotherapies. Finding evidence on the differential (cost)-effectiveness for this group of patients and the working mechanisms of change is important to improve the quality of care for this vulnerable group of patients.

**Objective:**

In this study, we will compare the differential (cost)-effectiveness of three individual psychotherapies: short-term psychodynamic supportive psychotherapy (SPSP), affect phobia therapy (APT) and schema therapy (ST). Although these psychotherapies are commonly used in clinical practice, evidence for the Cluster-C PDs is limited. Additionally, we will investigate predictive factors, non-specific and therapy-specific mediators.

**Methods:**

This is a mono-centre randomized clinical trial with three parallel groups: (1) SPSP, (2) APT, (3) ST. Randomization on patient level will be pre-stratified according to type of PD. The total study population to be included consists of 264 patients with Cluster-C PDs or other specified PD with mainly Cluster-C traits, aged 18–65 years, seeking treatment at NPI, a Dutch mental health care institute specialized in PDs. SPSP, APT and ST (50 sessions per treatment) are offered twice a week in sessions of 50 min for the first 4 to 5 months. After that, session frequency decreases to once a week. All treatments have a maximum duration of 1 year. Change in the severity of the PD (ADP-IV) will be the primary outcome measure. Secondary outcome measures are personality functioning, psychiatric symptoms and quality of life. Several potential mediators, predictors and moderators of outcome are also assessed. The effectiveness study is complemented with a cost-effectiveness/utility study, using both clinical effects and quality-adjusted life-years, and primarily based on a societal approach. Assessments will take place at baseline, start of treatment and at 1, 3, 6, 9, 12, 18, 24 and 36 months.

**Discussion:**

This is the first study comparing psychodynamic treatment to schema therapy for Cluster-C PDs. The naturalistic design enhances the clinical validity of the outcome. A limitation is the lack of a control group for ethical reasons.

**Trial registration:**

NL72823.029.20 [Registry ID: CCMO]. Registered on 31 August 2020. First participant included on 23 October 2020.

## Administrative information

Note: the numbers in curly brackets in this protocol refer to SPIRIT checklist item numbers. The order of the items has been modified to group similar items (see http://www.equator-network.org/reporting-guidelines/spirit-2013-statement-defining-standard-protocol-items-for-clinical-trials/).

## Introduction

### Background and rationale {6a}

Personality disorders (PDs) are complex mental health disorders associated with low levels of quality of life, high health care costs, and poor prognosis. PDs are clustered in three clusters: A, B and C (DSM-V, [3]). Cluster-C PDs, including avoidant, dependent and obsessive-compulsive PDs, are among the most common mental disorders in the general population, with reported prevalence rates of 3–9% [64, 94]. See Table 1 for brief definition of the clusters. In clinical populations, this cluster of PDs is most prevalent [4] and is associated with high levels of burden, societal dysfunctioning, low quality of life [89] and chronicity of many other common mental health disorders [73, 80]. Research in the field of PD has, to date, mainly excluded the Cluster-C PDs and focused on borderline PDs. Also, Cluster-C PDs are generally not included in international guidelines for PDs [49]. This means that a large group of patients has been neglected, and knowledge on how to treat them is lacking.

**Table 1 Tab1:** Brief definition of Cluster-A, B and C PDs

Cluster-A PDs (paranoid, schizoid and schizotypal PD) are considered to be the odd, eccentric disorders.	
Cluster-B PDs (borderline, narcissistic, histrionic, antisocial PD) are characterized by thoughts and emotions that are dramatic and overly emotional.	
Cluster-C PDs (avoidant, compulsive, dependent PD) are characterized by anxiety and fear (DSM-V, APA, 2013).	

Despite the scarcity of outcome studies, in routine clinical practice patients with (comorbid) Cluster-C PDs are frequently referred to mental health care and offered general treatments such as cognitive behavioural therapy or psychodynamic therapy. In order to obtain more evidence, this study compares the differential effectiveness of three individual psychotherapies for Cluster-C PDs: short-term psychodynamic supportive psychotherapy (SPSP), affect phobia therapy (APT) and schema therapy (ST).

#### Evidence from previous trials

To the best of our knowledge, only a few randomized clinical trials (RCTs) into individual treatment of Cluster-C PDs have been conducted [56]. In a large multicentre study (*N*=323), Bamelis et al. [11] compared the effectiveness of 50 sessions of schema therapy, open-ended clarification-oriented psychotherapy, and treatment-as-usual (TAU) in PD patients with mainly Cluster-C PD. They found ST to be superior to TAU and clarification-oriented psychotherapy on interview-based outcome.

The other four studies all consist of relatively small samples of 16 to 25 patients per treatment and considerable variations in doses and therapy forms. Emmelkamp et al. [33] found greater improvement in 20 sessions of cognitive psychotherapy in comparison with psychodynamic psychotherapy for avoidant PD (*N*=62). Svartberg et al. [93] found no difference between 40 sessions APT versus cognitive behavioural therapy for Cluster-C PDs (*N*=50). Hellerstein et al. [46] compared brief supportive psychotherapy with short-term dynamic psychotherapy (both 40 sessions) in 49 patients with mainly Cluster-C PDs, and found no significant differences between the therapies. Muran et al. [78] found significant differences only on some secondary outcomes that were not maintained at follow-up between 30 sessions psychodynamic therapy, brief relational therapy, and cognitive behavioural therapy for Cluster-C PDs (*N*=84). These few studies indicate that psychotherapies for Cluster-C are effective, with, except for the Bamelis et al. and Emmelkamp et al. studies, little differences between the various psychotherapy forms. However, the relatively small sample sizes of most studies limit the power to detect possible clinically relevant differences. No studies have been conducted comparing the effectiveness of SPSP, APT and ST for Cluster-C PD. Next, only the Bamelis study used an active control group, providing evidence for the unique therapeutic benefit of this therapy for Cluster-C PD. The other studies however did not use active control groups. This means the impact of the unique ingredients of these treatments for the Cluster-C PDs is still unclear.

### Explanation for the choice of comparators {6b}

#### Psychotherapies

In this study, we will compare schema therapy (ST), short-term psychodynamic psychotherapy (SPSP) and affect phobia therapy (APT). ST has gained interest worldwide in the treatment of PDs. Despite most research on ST for PDs has been focused on borderline PD, ST has also shown evidence in the treatment of Cluster-C PDs in clinical effectiveness, acceptability, and cost-effectiveness [9, 11]. Evidence for the effectiveness of ST has also been found for various anxiety and depression disorders [51, 72]. ST as delivered in our study is based on the Bamelis protocol [5, 6, 10].

A relatively wide range of group and individual psychodynamic therapies, long-term and short-term, have been evaluated mainly in mixed samples of personality pathology or borderline PD [37, 62]. In this study, we choose to study APT and SPSP. They are both time-limited psychodynamic therapies and include established interventions to address main problems related to Cluster-C pathology such as avoidance and dependence. In clinical practice APT is upcoming as a treatment for the Cluster-C PDs. It is developed by McCullough and has reformulated psychodynamic psychotherapy into a behavioural framework [53]. APT has been applied for treatment of various anxiety disorders, depression, and PDs. Empirical evidence of APT for (Cluster-C) PDs has been found in the earlier mentioned Svartberg study [93] and by Winston et al. [103].

SPSP is a psychodynamic psychotherapy that uses a supportive stance and techniques. It has been applied for depression with and without PD [60], focusing on depression in relation to inter- and intrapersonal patterns while taking into account etiologic longstanding personality vulnerabilities. SPSP has shown to be effective for depression in several RCTs [32]. In one of the first RCTs with SPSP [60], an effect on PD could be demonstrated independent from a concurrent improvement of depression. This is further corroborated in a current trial comparing SPSP to ST for patients with both depression and PDs [58]. The preliminary results indicate that these approaches could diminish both depression and PD pathology [59]. In our study, the SPSP protocol is slightly adjusted in particular to address personality pathology also in the absence of comorbid depression.

#### Process research

Understanding *why, how* and *for whom* a treatment works can offer insight how to ameliorate the treatment techniques and interventions to optimize its effectiveness [23]. This could be approached by studying predictors and therapy-specific and non-specific (common) working mechanisms. There are only a few studies on the potential predictors of differential outcome and the working mechanisms within Cluster-C PDs [1]. Lilliengren et al. [65] found that successful cases of psychotherapy for Cluster-C PDs were characterized by more engaged patients and unsuccessful cases by a more directive therapist stance. Some correlational process-outcome research has been done showing first support that change in some of the factors of the theoretical model of APT is related to outcome (for an overview see [53]). Analysis of the data of the Bamelis study suggests that two schema modes (i.e. the Healthy Adult and the Vulnerable Child) play a central role in the successive changes in the personality pathology [104]. The latter studies are based on differential theoretical backgrounds on psychotherapy for Cluster-C PDs. Process research based on a general Cluster-C theoretical model is lacking.

#### Potential mediators

In the research on mediators, general working mechanisms as well as specific working mechanisms are studied. In this study, specific working mechanisms for the three treatments SPSP, APT and ST are derived from the theoretical assumption about their effectiveness. In SPSP, the level of emotional and interpersonal insight is supposed to mediate outcome for personality factors. The assumption for APT is that restructuring of defence mechanisms (recognizing and learning to let go of dysfunctional defences), affect (ameliorating the experience and expression of adaptive emotions) and the self (ameliorating self-esteem) is mediating treatment outcome [96]. For ST, as mentioned before, Yakın et al. [104] have found that two schema modes, the Healthy Adult (integrated, wise and healthy functioning state) and the Vulnerable Child (state of anxiety, sadness, loneliness, or neglect/abuse), are central to the change process of personality pathology. Strengthening of the Healthy Adult mode and healing of the Vulnerable Child mode are hypothesized to reflect mechanism of change, not only in ST but also in other psychotherapies.

The influence of specific factors needs to be studied in the context of well-known common factors in psychotherapy. Numerous studies have demonstrated that the quality of the therapeutic alliance is a stable and relevant factor for change [38]. Zilcha-Mano [106] stresses the importance to differentiate between trait- and state-like components of alliance. The trait component refers to the patients’ general tendencies to form satisfying relationships. Clearly this also affects the relationship with the therapist. The state component describes the development of these tendencies or abilities of the patient through the interaction with the therapist. Thus the trait-like component could be considered as a general precondition for all therapeutic work. In contrast, the state-like component is assumed to be a potential discriminative curative factor, specifically related to either a therapy form or therapist. In addition, trait- and state-like alliance may play different roles in various therapy treatments. Comparing various psychotherapies allows us to disentangle potential differential effects of alliance in SPSP, APT and ST.

According to Kazdin [55], research on mechanisms of change needs to demonstrate a statistical association and a temporal relationship between treatment interventions, mediator and outcome, but also consistency and specificity of this mediator. Therefore, potential mediators and outcomes must be measured at multiple time-points during and after therapy, across the treatments [63]. These guidelines will be followed in the current study. Also, treatment interventions will be specified to explore the relationship between certain interventions, mediators and outcome.

#### Potential predictors

To gain more knowledge about what works for *whom*, potential predictors will be studied. We will investigate several general potential predictors (that may turn out to be moderators, i.e. differential predictors depending on treatment type): sociodemographic variables, subtype of PD, severity of psychiatric symptoms, severity of the PD. Next, after consultation of experts in the treatment of Cluster-C PDs, the following four specific potential predictors are defined.Childhood trauma: Childhood traumatic events are assumed at least partially to underlie the development of personality pathology, and adequately processing is helpful to reduce these problems [5, 6]. It has been identified as a negative predictor of treatment outcome for different psychiatric disorder [79],Level of autism traits: There is a high comorbidity and considerable overlap in symptoms between autism and PDs [69, 100]. Lugnegård et al. [70] found about half of the participants with an autism spectrum disorder (ASD) also met criteria for a PD, all belonging to Cluster-A or C. Effectiveness of psychotherapy for patients with PD and comorbid autism traits has not been studied, but Weston et al. [102] found lower effectiveness of treatment (cognitive behavioural therapy) of affective disorders within patients with ASD.Personality organization as defined by Kernberg [57]: The level of personality organization is defined by three domains: identity, primitive defence mechanisms, and reality testing. The severity of the personality pathology is ranging from neurotic personality organization to borderline personality organization to psychotic personality organization, the latter one being the most severe group of patients. Higher levels of personality organization are related to better treatment outcome [61]. Overall, in Cluster-C PDs, higher levels of personality organization were found than for Cluster-A or B PDs [29]. Until now, personality organization within Cluster-C patients and its impact on outcome has not been investigated.Vulnerable narcissism: Vulnerable narcissism is mainly manifested in the avoidant and obsessive-compulsive PD [76, 81] and is related to avoidant attachment and maladaptive, impulsive and avoidant ways of coping with stress [54]. No studies are available on the effectiveness of patients with Cluster-C PD and vulnerable narcissism, but vulnerable narcissism might be related to negative treatment outcome.

### Objectives {7}

The primary aim of this study is to compare the effectiveness and cost-effectiveness of the three individual treatments (SPSP, APT and ST) for Cluster-C PDs. The primary outcome of this superiority study is the severity of Cluster-C PD. We will compare the slopes over time of the three treatments from 0 to 12 months, with assessments of Cluster-C PD severity taking place at baseline, 1, 3, 6 and 9 months. Additionally, we will research differences between the outcomes of the three treatments at 18, 24 and 36 months follow-up. No hypothesis was formulated about the direction of a difference.

The second aim of this study is to explore working mechanisms by focussing on therapy-specific factors in the context of the contribution of common factors across psychotherapies. Selected therapy-specific factors are as follows: therapy-specific interventions; insight for SPSP; change in affect, defence style, perception of the self for APT; change in schema modes for ST. Working alliance is the non-specific factor being investigated.

The third aim is to identify general and specific predictors. Potential moderators will be studied exploratively. Firstly, we hypothesize that patients with relatively more childhood trauma will benefit more from ST than SPSP and APT, because of the use of imaginary rescripting, an evidence-based trauma processing technique [35, 83]. Secondly, we expect that patients with more severe personality pathology (e.g. borderline personality organization (Kernberg, [57]) will profit more from ST or SPSP than APT. This is because these therapies are developed and have proven their effectiveness for a broader range of PDs [60, 88], whereas APT is originally designed for the Cluster-C/neurotic population [25].

The relationship between specific treatment interventions, mediators and outcome will also be explored. Therapists will indicate per session which of the core interventions per treatment they have applied in their sessions. The hypothesis is that certain interventions will be stronger connected to mediators and outcome than others. For example, experiential techniques (imagery rescripting, multiple chair technique) for ST; adequate support for SPSP; facilitation of expression of emotions for APT.

With the results of this study, we aim to enlarge the evidence-based support for treatments of the Cluster-C population and contribute to the improvement of the quality of care for this vulnerable and scientifically relatively neglected group of patients [49].

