### Trial design {8}

The I-FORCE study is a mono-centre RCT with three parallel treatments: (1) SPSP; (2) APT; (3) ST. The patient allocation ratio is 1:1:1. All treatments will provide 50 sessions, the first 32 sessions twice a week (4–5 months), the other 18 sessions weekly (4–5 months). I-FORCE is a pragmatic ecologically valid RCT, which means it will be conducted in the routine specialized clinical setting. Characteristics for a pragmatic trial are the use of minimal exclusion criteria and low barriers to patient participation. Waiving a comparison group with no treatment guarantees inclusion into an effective treatment and minimizes unwillingness to be randomized [35]. This means patients with a wide range of psychiatric comorbidity will be included in this study. Also, use of psychopharmacological medication is not a reason for exclusion.

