### Participant timeline {13}

#### Sample size {14}^3^

First, the required sample size was calculated to compare the three types of active treatments. Three pairwise comparisons will be conducted between the active treatment arms (ST vs. APT, ST vs. SPSP; APT vs. SPSP). We want to detect a medium effect size (*f*=0.11) in a pairwise comparison of pre-post change between two active treatment arms, equivalent to *f*(*v*)=.2460 and Cohen’s *d*=.492, with Bonferroni-corrected *p* = 0.0167, a power of 0.80 and within-person correlation coefficient=0.60, for which 88 patients are needed per arm. Because three types of therapies will be compared, 3 × 88 = 264 participants are needed to perform three pairwise comparisons. We chose a medium effect size (f=0.11^4^) since this would also be a clinically meaningful difference, as opposed to a smaller effect size.

The correlation of 0.60 is an educated guess of the correlation between repeated assessments based on the previous RCTs the authors conducted.

The final analysis will be conducted with mixed regression on time series: the change in slope over time between two treatments. Because power analysis for mixed regression are complex and based on complex assumptions about the covariance-structure, a simplified approach was chosen by conducting a power analysis on the pre-post change.

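### Month 12 is missing from the visit list for the primary 0–12 month slope comparison and should be added

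*Protocol article*

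**What the plan says.** The protocol article, Objectives {7}, sets the primary comparison: "We will compare the slopes over time of the three treatments from 0 to 12 months". The same sentence then names the contributing visits: "with assessments of Cluster-C PD severity taking place at baseline, 1, 3, 6 and 9 months". The next sentence covers the later period: "we will research differences between the outcomes of the three treatments at 18, 24 and 36 months follow-up".

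The abstract (Methods) gives the schedule for the trial as a whole: "Assessments will take place at baseline, start of treatment and at 1, 3, 6, 9, 12, 18, 24 and 36 months". Table 3, which would show the visits at which the ADP-IV is taken, is not available in the text at hand.

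Sample size {14} says that the final analysis is a difference in slope from mixed regression, but that for planning "a simplified approach was chosen by conducting a power analysis on the pre-post change". Its inputs are "equivalent to *f*(*v*)=.2460 and Cohen’s *d*=.492" and "with Bonferroni-corrected *p* = 0.0167, a power of 0.80 and within-person correlation coefficient=0.60, for which 88 patients are needed per arm". It does not name the month of the post value. The Limitations section says the sample was not inflated for dropout and relies on repeated measurements between pre-treatment and post-treatment to make up for the loss.

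**The concern.** The Objectives section gives the slope a 12-month window but lists visits for nine months of it. With follow-up comparisons beginning at month 18, the 12-month value of the primary outcome belongs to no stated comparison. That value closes the stated window and is the natural post value for the power calculation, since treatment lasts at most one year.

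Two things are at stake if the list is applied literally. First, the latest visit carries the most information about a slope, so dropping it costs precision in a trial with no allowance for dropout. Second, a 0–12 month statement would rest on a line fitted to months 0–9. The session schedule changes within the year: "the first 32 sessions twice a week (4–5 months), the other 18 sessions weekly (4–5 months". Whether the arms diverge at a steady rate throughout is therefore an open question.

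**Working it through.** **Reproducing the plan's figure.** Inputs from Sample size {14}: f = 0.11, correlation 0.60, two measurements, alpha 0.0167, power 0.80.

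- f(V) = f × √(m/(1−ρ)) = 0.11 × √(2/0.4) = 0.2460, and d = 2 × 0.2460 = 0.492. Both match the text.
- A two-sided two-sample test (noncentral t) gives power 0.795 at 87 per arm and 0.8005 at 88. The stated 88 is reproduced. A one-sided test would need 73, so two-sided is the reading that fits.

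**Moving to the slope.** The d of 0.492 is in units of the SD of change. In units of the outcome SD the difference is 0.492 × √(2 × (1−0.6)) = 0.44. If it builds up linearly and is complete at month 12, the slope difference is 0.44/12 = 0.0367 SD per month.

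With a constant correlation of 0.60 between all visits and a free intercept in each arm, SE = √(2(1−ρ)/(Sxx × n)), where Sxx is the sum of squared deviations of the visit times. The critical value for two-sided 0.0167 is 2.393.

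- Visits 0, 1, 3, 6, 9: Sxx = 127 − 19²/5 = 54.8. SE = √(0.8/(54.8 × 88)) = 0.01288. z = 0.0367/0.01288 = 2.85. Power = Φ(2.85 − 2.393) = 0.675.
- Visits 0, 1, 3, 6, 9, 12: Sxx = 271 − 31²/6 = 110.8. SE = 0.00906. z = 4.05. Power = 0.95.
- With visits ending at month 9, 80% power would need about 88 × ((2.393 + 0.842)/2.85)² ≈ 114 per arm.

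**How far this depends on assumptions.** The protocol does not fix the correlation pattern, the shape of divergence or the month at which the effect is defined. Power at 88 per arm, normal approximation:

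| Assumption | Visits to month 9 | Month 12 added |
|---|---|---|
| Base case above | 0.675 | 0.95 |
| Common baseline intercept | 0.75 | 0.97 |
| Constant correlation 0.5 (same 0.44 SD difference) | 0.56 | 0.89 |
| Constant correlation 0.7 (same 0.44 SD difference) | 0.81 | 0.99 |
| Correlation decaying to 0.60 at 12 months (AR(1)) | 0.64 | 0.81 |
| Random slopes, 25% of change variance | 0.71 | 0.92 |
| Random slopes, 50% of change variance | 0.74 | 0.88 |
| Random slopes, 100% of change variance | 0.81 | 0.81 |
| Baseline and last visit only | 0.52 | 0.81 |
| Full difference already reached at month 9 | 0.92 | not computed |

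Month 12 raises power in every row computed both ways except one. When all variance of change lies in true individual slopes, the two designs are equal. A much steeper decay (0.60 over three months) would give 0.26 without month 12 and 0.43 with it. It would also bring the pre-post test down to 0.43, which contradicts the plan's own 0.80, so it is left out of the range.

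**The case against.** The strongest reply is that a 12 was dropped from a sentence and nothing more. Much of the article supports this:

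- The Objectives sentence itself gives a 12-month window and does not say that the listed visits are the only ones.
- The post-trial care section places month 18 six months after the end of treatment, which makes month 12 the post-treatment point.
- For another measure, level of discourse, the article lists months 1, 3, 6 and 9 and then the end of treatment.
- The statistical methods section says the mixed model uses all available data.
- The Limitations argument about dropout presupposes a post-treatment value.

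This stands, and it rules out a stronger reading that a reader might infer: that the plan deliberately excludes the 12-month outcome. The reply does not remove the conflict, however. The abstract's schedule covers all instruments and Table 3 is not visible, so no available text states that the 12-month ADP-IV enters the primary model.

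The reply also limits the power figure. Besides the protocol's correlation, the 0.67 needs compound symmetry, linear divergence and a difference complete only at month 12. Sessions as scheduled would end at about 8 to 10 months, so an earlier full difference is conceivable, and power would then be 0.92 without month 12. Setting 0.67 beside the stated 0.80 also compares a slope test with a pre-post test. The like-for-like pair is 0.67 and 0.95.

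A reader might further infer that the trial will report a projected 12-month difference, distorted if the arms improve at different speeds. The article plans a difference in slopes and no projected value, and the size of any distortion would depend on a curve that the documents do not give.

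**Conclusion.** The Objectives section contains an internal inconsistency in the primary objective: a 0–12 month slope, a visit list ending at month 9, and follow-up starting at month 18. It is probably an omission, but it concerns which data define the primary estimate and should be corrected.

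The consequence is conditional on the list being followed literally. Power for d = 0.492 reached at month 12 would then be about 0.67 instead of about 0.95, assuming constant correlation 0.60 and linear divergence, with about 0.52 to 0.92 under the other assumptions considered. The documents do not support saying that the trial as planned has 67% power, and the stated 88 per arm is correct for the pre-post comparison it describes.

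Nor does the inconsistency show that the slope is the wrong primary contrast. Under constant correlation and complete data, a categorical-time contrast from baseline to month 12 is the pre-post contrast. If change is linear, replacing the slope with it would lower power from about 0.95 to 0.80.

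**What to change.** Amend Objectives {7} so that the primary 0–12 month slope model uses the assessments at baseline and at 1, 3, 6, 9 and 12 months, in agreement with the abstract's schedule and the pre-post basis of the sample size. Check that Table 3 shows the ADP-IV at month 12. It would also help to state in Sample size {14} that the post value is the 12-month one, if that is what was meant.

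The baseline-to-12-month difference with time as a categorical factor can be reported as a sensitivity analysis for non-linear change, with the slope kept as primary.

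The cost is wording alone, since the 12-month assessment is already scheduled. No change to the sample size follows from this point.
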